#### Sampling procedures

Convenience sampling was used to select nursing homes for the study. NBNH administrators and directors of nursing were contacted by email to determine interest in study participation.

Convenience sampling will also be used to recruit health care providers, older adults, and family members of older adults from study nursing homes. A recruitment poster for resident and family member surveys will be posted in study nursing homes and a communication will be sent to families and substitute decision makers by regular mail or email using the study site contact list. Health care providers and study site staff will be recruited to register for MedReviewRx by placing written recruitment notices in their nursing home site mailbox and/or by email. All pharmacists, nurses, nurse practitioners, and physicians providing care at the participating nursing home will receive recruitment emails for MedReviewRx feedback surveys. Members of healthcare teams at the study sites will be recruited to participate in interviews to explore overall experience with the research project.

#### Variables under investigation include:

A)Patient demographics (date of admission to LTC, age, sex, gender, nursing home identifier, medical, and psychiatric conditions documented in the interRAI LTCF assessment, and date of discharge from LTC if applicable).B)Medication use data: absolute number of medications, number of PIMs, proportion of all medications that are PIMs, and type of deprescribing opportunities identified (PIMs that are high risk, intermediate risk, or of little added value).C)Safety data: death, fracture, fall, use of restraints, transfer to hospital, change in functional status based on interRAI activities of daily living (ADL) scores. Episodes of delirium based on responses to questions in Section C of the interRAI LTCF assessment form (periodic disordered thinking or awareness and acute change in mental status from a person’s usual functioning).D)D)Health care provider experience with MedReviewRx and MedSafer deprescribing information as described in the user feedback surveys and the acceptability and feasibility survey.E)Nursing home evaluation of the implementation toolkit.F)Patient and caregiver attitudes about deprescribing.

### Plans to promote participant retention and complete follow-up {18b}

Participants are automatically enrolled when targeted nursing homes agree to take part in the study.

### Data management {19}

Patient demographics and safety data is entered in the interRAI LTCF assessment software by nursing home staff as part of usual care. Medication information will be obtained from nursing home MARs and entered in section N1 of the interRAI LTCF assessment software by nursing home staff or a trained research assistant. Research assistants who enter medication data will receive training on how to enter medication information into Momentum LTCF assessment software. Patient demographics, medication use, and safety data will be extracted from the LTCF interRAI assessment software and loaded into MedReviewRx by the study site contact (or designate) at each nursing home.

### Confidentiality {27}

MedReviewRx will de-identify the data and transmit data sets to MedSafer. Multiple safeguards have been put in place to protect this data. Data sets do not contain patient-specific information. Age is transmitted rather than date of birth, and a unique identifier is assigned to each patient data set. MedSafer is unable to identify patients however the unique identifier allows MedReviewRx and MedSafer applications to anonymously communicate about specific patients through an application programming interface (API). Data sets will be analyzed by the MedSafer software program. Files containing one or more targeted PIM and associated triggering condition(s) will have deprescribing opportunities flagged and returned to MedReviewRx. MedReviewRx will link the unique identifier to the correct nursing home patient and translate the MedSafer analysis into an output for review by their health care team. A message will also be displayed by MedReviewRx if there are no deprescribing opportunities identified for a data set. MedReviewRx transmits and stores data using a secure web-based system which was designed by Missing Links Technology (MLT) under the supervision of the New Brunswick Community College (NBCC). The MedReviewRx system safeguards personal health information (PHI) that it collects, processes, and disseminates within trusted and authorized circles of care and ensures the confidentiality and privacy of the PHI. Each study site using MedReviewRx has site-specific policies and procedures with respect to privacy and confidentiality of PHI.

Data from User Feedback Surveys and Acceptability and Feasibility Surveys and survey responses collected from the rPATD questionnaires completed via Lime Survey will be extracted into excel sheet format. Survey data collected from paper surveys or telephone surveys will be entered into the excel database by a research assistant. Research assistants will be provided with templates for excel data entry and trained on how to complete the template. A minimum of 5% of the research assistant data entry will be audited for accuracy and completeness by the CIRA research manager or designate. Interview data will be recorded and transcribed verbatim by research assistants. Interview recordings will be deleted after transcripts have been validated. Study data (PIMs, survey responses, interview transcripts) will be stored in password-protected, members only secure cloud-based study sites hosted within Canada. Study data will only be accessible to the study research team and the CIRA research manager. On study closure, after final data analysis is completed, study data will be downloaded to a password-protected study folder on the YCC secure network and the cloud-based study site will be permanently deleted. Study data will be stored for 7 years and then destroyed in accordance with YCC/CIRA policies and procedures.

### Plans for collection, laboratory evaluation, and storage of biological specimens for genetic or molecular analysis in this trial/future use {33}

No biological specimens were collected as part of this trial.

Data analysis plan

This mixed methods study will employ both qualitative and quantitative data analysis.

### Statistical methods for primary and secondary outcomes {20a}

Analysis of the primary outcome will be conducted using the stepped wedge function in Stata v. 15 or a similar statistical program. The primary analysis will use a Generalized Liner Mixed Model with a logit link, treating time and intervention as fixed effects, and cluster as a random effect. This information has been added to the manuscript.

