### Sample size {14}

Based on the Canadian Institute for Health Information’s report, titled “Drug Use Among Seniors in Canada, 2016”, we expect that about 70% will be taking one or more PIMs. This yields an average cluster size of 175 for patients with at least 1 PIM. Uptake of deprescribing using the MedSafer report in acute care studies ranges from 8 to 25% [13] over usual care. Conservatively, we think we can increase the proportion of patients with 1 or more PIM deprescribed from a baseline rate of 10 to 20% (absolute increase of 10% or a number needed to treat of 10). Using the Shiny CRT calculator [15], we estimate that we will have at least 72% power to detect this difference under assumptions of cluster autocorrelation of 0.8 and a within period intra-cluster correlation (ICC) 0.05. This increases to 96% power if the ICC is 0.02.

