### Recruitment {15}

Nursing homes may experience 20 to 30% patient turnover each year due to deaths; therefore, the total number of nursing home residents who have at least one interRAI LTCF assessment during the study period is approximately 1000. For the purposes of analysis, only the initial closed cohort will be included in the study. New residents will not be analyzed in the current study. All homes have agreed to participate in the study and an individual waiver of consent has been granted by the Horizon Health Network Research Ethics Board.

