#### Impact on PIMs

The impact on PIMs will be determined by the proportion of nursing home residents who have one or more PIMs reduced or stopped after the treating physician receives a MedSafer report. This outcome will be measured by using unique identifiers to compare medication data from sequential interRAI data sets. PIMs identified in the baseline data set will be compared with the next data set (3 months later) transmitted with that unique identifier to determine if any of the PIMs has been stopped (no longer listed) or if a PIM dose has been reduced. This process will continue for the study duration. All statistical comparison will be performed via STAT v 15 (or equivalent) and the stepped wedge function will be used for the primary outcome (proportion of patients with one or more PIMs deprescribed over the study period).

At the end of the study, subgroup analysis will be conducted on the PIM data to explore PIM use based on sex, gender, and geographic location.

Co-primary outcome:
User experience with MedSafer reports and MedReviewRx.

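### The stated primary model omits the entry PIM count, on which the outcome depends by construction; adjusting for it would bring a small, nearly free gain in power

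*Protocol article*

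**What the plan says.** The protocol article, under Statistical methods for primary and secondary outcomes {20a}, specifies a generalised linear mixed model with a logit link, "treating time and intervention as fixed effects, and cluster as a random effect". No resident characteristic is named. The two sensitivity analyses under Methods for additional analyses {20b}, a fully fixed-effects model and permutation tests, add none.

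Under Impact on PIMs, the outcome is "the proportion of nursing home residents who have one or more PIMs reduced or stopped", judged by comparing consecutive quarterly data sets. Eligibility requires at least one PIM.

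The variables to be collected include "Medication use data: absolute number of medications, number of PIMs, proportion of all medications that are PIMs", as well as age and sex. The participant timeline shows medication data collected from months 1–3, when all three clusters are in control.

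Only the initial closed cohort is analysed. Recruitment {15} warns that "Nursing homes may experience 20 to 30% patient turnover each year due to deaths", and residents who die or are hospitalised are censored. Trial status promises a detailed statistical analysis plan before enrolment; it is not among the documents at hand.

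**The concern.** A yes/no outcome defined as any PIM stopped or reduced is easier to reach for a resident with eight PIMs than for a resident with one. The count therefore carries prognostic information by the way the outcome is built. The trial already holds the value, and holds it from before any cluster switches. A model without it leaves explainable resident-level variation in the comparison.

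Power is what is at stake. The plan itself claims only "at least 72% power to detect this difference under assumptions of cluster autocorrelation of 0.8 and a within period intra-cluster correlation (ICC) 0.05". With three clusters and four quarters, a gain that needs no new data is worth taking. A second, lesser matter is that the closed cohort shrinks through deaths. If residents with many PIMs are lost faster in one cluster than in another, the resulting change in case mix is not captured by the time or cluster terms.

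**Working it through.** **Inputs from the protocol article.** Three clusters and four three-month periods; responders 10% under control and 20% under intervention; "This yields an average cluster size of 175 for patients with at least 1 PIM"; cluster autocorrelation (CAC) 0.8; ICC 0.05 or 0.02; turnover of 20–30% a year, which is 1 − 0.80^¼ = 5.4% to 1 − 0.70^¼ = 8.5% a quarter.

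**Assumptions, because the article gives no figure.** Two-sided alpha 0.05; the distribution of PIM counts; an equal and independent chance q that each PIM is stopped or reduced; the individual autocorrelation (IAC).

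**Step 1: the plan's own power.** Let σ² = (0.1×0.9 + 0.2×0.8)/2 = 0.125 and m = 175. The cluster-period means have covariance [σ²·ICC·CAC + σ²(1−ICC)·IAC/m]·J + [σ²·ICC·(1−CAC) + σ²(1−ICC)(1−IAC)/m]·I, where J is the all-ones matrix and I the identity. With period fixed effects, power = Φ(0.10/√v − 1.96), where v is the variance of the estimated effect.

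| Variant | ICC 0.05 | ICC 0.02 |
|---|---|---|
| Stated in the article | 72% | 96% |
| Cross-sectional, IAC 0 | 56.9% | 78.1% |
| Closed cohort, IAC 0.80 | 70.4% | 95.7% |
| Closed cohort, IAC 0.90 | 72.4% | 97.3% |

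The stated figures are reproduced within about two points by a closed cohort with a high IAC. The article does not state that IAC.

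**Step 2: how the outcome depends on the count.** P(responder | k PIMs) = 1 − (1−q)^k. With zero-truncated Poisson counts of mean 3, q = 0.035 gives 10% overall and q = 0.074 gives 20% overall.

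| k | Control | Intervention |
|---|---|---|
| 1 | 3.5% | 7.4% |
| 3 | 1 − 0.965³ = 10.1% | 1 − 0.926³ = 20.6% |
| 6 | 1 − 0.965⁶ = 19.2% | 1 − 0.926⁶ = 36.9% |

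Across truncated-Poisson means of 1.5 to 5, the count explains about 2–5.5% of the outcome variance.

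**Step 3: gain with resident-level noise only.** These are logistic models for the 3×4 wedge with cluster and period terms, fitted without and with log(k).

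| Counts assumed | z without | z with | Gain in z |
|---|---|---|---|
| Truncated Poisson, mean 3 (expected-value fit) | 3.18 | 3.24 | 1.9% |
| Truncated Poisson, mean 2.7 (simulation) | 3.13 | 3.20 | 2.2% |
| Truncated Poisson (separate simulation) | 3.25 | 3.32 | 2.2% |
| Overdispersed, mean 3.7, SD 2.9 (simulation) | 3.21 | 3.35 | 4.4% |
| Overdispersed (separate simulation) | 3.15 | 3.31 | 5.1% |

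The extremes among all settings tried were 1.3% (3.18 to 3.22; truncated Poisson, mean 5) and 5.6% (3.22 to 3.40; overdispersed, mean 5.0, SD 4.5).

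The z rises because the coefficient grows, not because the standard error falls. In one pair of simulations the log odds ratio went from 0.804 to 0.838 with the standard error going from 0.264 to 0.269 (truncated Poisson). With overdispersed counts it went from 0.825 to 0.896, and the standard error from 0.263 to 0.274.

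**Step 4: gain under the plan's own correlations.** The resident share of the cell error is [(1−ICC)/m] / [(1−ICC)/m + ICC(1−CAC)].

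- ICC 0.05: 0.00543/(0.00543 + 0.010) = 0.35.
- ICC 0.02: 0.0056/(0.0056 + 0.004) = 0.58.

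Only that share can shrink. Removing a fraction R² of the resident-level variance in Step 1 gives:

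| R² | Cohort, IAC 0.8 (ICC 0.05 / 0.02) | Cross-sectional (ICC 0.05 / 0.02) |
|---|---|---|
| 0 | 70.4% / 95.7% | 56.9% / 78.1% |
| 2% | 70.5% / 95.7% | 57.2% / 78.6% |
| 5% | 70.6% / 95.8% | 57.6% / 79.2% |
| 10% | 70.8% / 96.0% | 58.3% / 80.4% |

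At R² of 2–5% the gain is 0.1–0.2 points in the cohort variant and 0.3–1.1 points in the cross-sectional one. If all of the explained variance is taken from the stable between-resident part of the cohort model, the gain is practically nil (70.38% against 70.39% at ICC 0.05, even with R² = 10%).

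**Step 5: drift, with no true effect.** With 7% quarterly deaths in every cluster, the unadjusted odds ratio is 1.000. With quarterly deaths of 12/7/4% across clusters, in either order, and death risk rising 10% or 30% per PIM, it is 0.992 to 1.009. The target odds ratio is (0.20/0.80)/(0.10/0.90) = 2.25. In one further simulated scenario, where one cluster selectively lost high-PIM residents in one quarter, the log odds ratio was +0.04 unadjusted and −0.02 adjusted. Monte Carlo error there is about 0.30/√800 = 0.011 to 0.30/√400 = 0.015, so it shows no clear reduction in bias, and nothing here rests on it.

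**The case against.** The strongest reply is that a journal article gives a model's structural terms and leaves covariates to the analysis plan. Time and intervention fixed with cluster random is a conventional stepped-wedge model and is valid without covariates. This stands in so far as the article contains no contradiction and the unseen plan may already adjust. But the article does state a definite primary model and its two sensitivity analyses, so proposing a better model is a comment on what is stated and not a request for missing detail.

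The second reply is that the benefit is small and partly a change of target, since the adjusted odds ratio is conditional on the count (about 2.30–2.33 against 2.25). Both parts are correct, and they limit the weight of the point.

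A reader might infer more: that deaths in the closed cohort leave case-mix drift in the treatment effect. The documents do not support that. The fixed time effects absorb drift common to all clusters, and the cluster effect absorbs stable differences. Only cluster-specific drift remains, and it moved the null odds ratio by less than 1% in the 12/7/4% scenarios. A reader might also call PIM count the strongest predictor available, or assume that age and sex would help as well. The documents give no data on predictors, and no calculation here tests age or sex.

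**Conclusion.** The point holds as a modest, low-cost improvement to the stated primary model. It is not an error that threatens the result. The entry PIM count is linked to the outcome by construction, is collected anyway, and is measured before any cluster switches. Adjusting for it is worth about 2–5% in z with resident-level noise only, and roughly 0.1–1 percentage point of power under the plan's ICC and CAC. The low end applies to the closed-cohort variant, which is the one that comes close to the stated 72% and 96%. Protection against cluster-specific drift is a minor added benefit.

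These sizes rest on assumed PIM distributions, an equal and independent chance per PIM, and an assumed IAC. More dispersed counts would raise the gain: at R² = 10% it is about 0.4 points in the cohort variant and 1.4 to 2.2 points in the cross-sectional one. A chance per PIM that falls steeply as the count rises would lower it.

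**What to change.** Add to the primary mixed model the log of the number of PIMs in the resident's first (months 1–3) data set. Fix it at entry and do not update it each quarter, because later counts can be changed by the intervention. Age and sex may be added but are optional. Keep the model without covariates as a named sensitivity analysis. Report a standardised risk difference beside the odds ratio; this also matches the ten-percentage-point difference on which the trial is sized.

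The cost is a sentence or two in the statistical analysis plan and no new data. The one small downside is that the adjusted odds ratio is conditional on the entry count, which the standardised risk difference addresses. The change should be made before enrolment, when the article says the analysis plan will be complete, so that the adjustment is clearly prespecified.

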### Interim analyses {21b}

There is no planned interim analysis.

### Methods for additional analyses (e.g., subgroup analyses) {20b}

Subgroup analyses will be conducted using the stepped wedge function in Stata v.15 or a similar statistical program. We will also perform 2 sensitivity analyses that will include a completely fixed effects model as well as non-parametric permutation tests. This will address any concerns related to the low number of clusters.

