### Intervention description {11a}

Estimated study duration is 18 months, and the effectiveness component of the study will use a deployment strategy which approximates a stepped wedge cluster randomized trial (SW-CRT). This design has many advantages and is considered the most robust type of study design for pragmatic quality improvement interventions. Each cluster will contribute a control period. Subsequently, at each of 3 pre-defined time periods, one cluster will be randomly assigned to transition from control to intervention. In this way, all clusters act as an internal control (before and after) as well as a contemporaneous control for the other clusters (external control). The study is composed of three clusters and each cluster contains the following number of beds: Cluster A 218, Cluster B 314, and Cluster C 272.

InterRAI Long-Term Care Facilities (LTCF) assessments are standardized for nursing home residents. These assessments are used to help identify health issues among residents, develop care plans, and monitor changes in the health of LTC residents. InterRAI LTCF assessments are conducted quarterly for every person living in a nursing home in New Brunswick. These assessments contain sociodemographic information, medical diagnoses, information on medications used by the resident, and variables which describe cognitive and physical function. The interRAI LTCF assessment form is completed by gathering input from the care team and responses are inputted electronically into Momentum Healthware (Momentum) software by nurses or interRAI coordinators.

MedSafer is a computer program which cross-references medical conditions, ICD-10 diagnosis codes, and medication drug identification numbers (DINs) to generate a deprescribing opportunities report that can be used by the prescriber as a roadmap for a comprehensive prescription check-up.

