### Sequence generation {16a}

Computer-generated random numbers were used in order to generate the allocation sequence of the clusters.

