In terms of our study design, we adopted a SW-CRT design. This study design addresses issues with seasonality and allows all clusters to participate in the intervention, which is an advantage when the intervention is related to quality improvement, and is appropriate for this study in several ways [17]. First, the SW-CRT design provides an opportunity for all participating nursing homes to receive the intervention at different time-points during the intervention period. This allows a staged implementation which helps when there are limited personnel to support the study (but from the research team and at the individual homes) while at the same time ensuring the quality of implementation. Third, the study design allows an estimation of the intervention effects using both a between- and within-cluster comparison. This unidirectional crossover design combines elements of before-after studies with cluster randomization and is an efficient design for answering the research question [18]. Moreover, stepped wedge trials can have a statistical advantage over parallel cluster randomized trials [19] [20]. The stepped wedge design is more efficient than a parallel group design as it requires a substantially smaller sample size.

We are using a cluster design to avoid contamination at the level of the home. The intervention involves a component of learning/teaching to the prescriber. If residents were randomized at the individual level within the same home, there is risk of contamination. Most homes have only a couple of prescribers. The intervention is directed at the level of the prescriber and so with time, they may learn that a certain medication is inappropriate, which risks contaminating participants who are randomized to the control. By randomizing at the level of a home, this minimizes this form of contamination.

Challenges in conducting the study are currently being faced. Firstly, the present pandemic era created by the novel COVID-19 has deprived our participating sites of their usual financial and human resources, which were allocated to battle the virus. Some of our homes even faced an outbreak of the virus among their residents, which put a halt on their research operations in order to fully mobilize their resources. Because every site is in its own unique situation, guidance and support from the study team will be tailored individually to each of those sites.

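### The permutation test and fixed-effects model do not dispose of the few-clusters problem: with three clusters the permutation p-value cannot fall below 1/6, and the fixed-effects model still omits cluster-by-period variation

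*Protocol article*

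**What the plan says.** Methods for additional analyses {20b} names two sensitivity analyses alongside the primary model: a completely fixed-effects model and "non-parametric permutation tests. This will address any concerns related to the low number of clusters".

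The design they must serve is set out elsewhere in the article:

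- Intervention description {11a}: "The study is composed of three clusters", and "at each of 3 pre-defined time periods, one cluster will be randomly assigned to transition from control to intervention".
- Sequence generation {16a}: "Computer-generated random numbers were used in order to generate the allocation sequence of the clusters".
- Participant timeline {13}: three clusters and four quarters, with one cluster crossing over at each of the last three quarters.
- Statistical methods {20a}: the primary model is a logit mixed model with time and intervention fixed and cluster random. No cluster-by-period term is described.
- Sample size {14}: "This yields an average cluster size of 175 for patients with at least 1 PIM", an improvement "from a baseline rate of 10 to 20" percent, and "cluster autocorrelation of 0.8 and a within period intra-cluster correlation (ICC) 0.05". Stated power is at least 72%, or 96% at ICC 0.02.
- Recruitment {15}: only the initial closed cohort is analysed.

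One sentence points to a different unit. The Discussion says "By randomizing at the level of a home, this minimizes this form of contamination".

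**The concern.** The article presents these two analyses as its protection against having very few clusters, and says they settle the matter. This is a positive claim about named methods, not a detail left for later.

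A permutation test re-assigns the randomised units to the rollout order, so its resolution is limited by the number of possible orders. Three units give very few. The fixed-effects model swaps the cluster random effect for cluster indicators. That removes one small-sample difficulty, but residents within a cluster and quarter are still treated as independent once cluster and quarter are fitted. The sample size section assumes otherwise: a cluster autocorrelation below 1 means that clusters drift from quarter to quarter.

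What is at stake is interpretation. Agreement between the mixed and fixed-effects models could be read as robustness, and a permutation p of 0.167 as contradiction. Neither reading would be safe.

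**Working it through.** **Inputs.** From the article: 3 clusters, 4 quarters, one crossover per step, m = 175 per cluster, 10% versus 20%, cluster autocorrelation (CAC) 0.8, ICC 0.05 or 0.02, closed cohort. Assumed, because not stated: two-sided 5% level, and individual autocorrelation (IAC) between 0 and 0.8.

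**1. The stated power.** Generalised least squares on cluster-quarter means, with outcome variance averaged over arms, (0.09 + 0.16)/2 = 0.125, and a normal approximation. With a closed cohort, IAC 0.8 and decaying correlation, the standard error at ICC 0.05 is 0.0392. Power is Φ(0.10/0.0392 − 1.96) = 72.3%, and 96.1% at ICC 0.02. Exchangeable correlation gives 70.4% and 95.7%. So the stated 72% and 96% are reproduced. A cross-sectional version gives 56.9% and 78.1% and does not match.

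**2. Permutation test.** Orders: 3! = 6. Smallest attainable p: 1/6 = 0.167, for any test statistic and any effect size. Full enumeration within simulated trials gave no p-value at or below 0.05 in any scenario, including a true 10% versus 20% effect.

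If five homes had been allocated individually, and if the split were 2/2/1 (the article does not give it), the count would be 5!/(2!·2!·1!) = 30, with a floor of 1/30 = 0.033. Only the single most extreme order could then reach 5%.

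**3. Fixed-effects model.** Total sum of squares of the treatment indicator over the 12 cells is 3. Removing the cluster part (0.5) and the quarter part (1.667) leaves 0.833, so the variance multiplier is 1/0.833 = 1.2. On the proportion scale, with outcome variance σ² and exchangeable correlation:

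- Variance the model assumes: 1.2·(1 − ICC)σ²/m
- Actual variance: 1.2·[ICC(1 − CAC)σ² + (1 − ICC)(1 − IAC)σ²/m]
- Ratio: R = (1 − IAC) + m·ICC(1 − CAC)/(1 − ICC)
- Type I error: 2[1 − Φ(1.96/√R)]

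The second term of R is 175 × 0.05 × 0.2/0.95 = 1.842 at ICC 0.05, and 175 × 0.02 × 0.2/0.98 = 0.714 at ICC 0.02.

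| ICC | IAC | R | Type I error |
|---|---|---|---|
| 0.05 | 0 | 2.842 | 0.245 |
| 0.05 | 0.8 | 2.042 | 0.170 |
| 0.02 | 0 | 1.714 | 0.134 |
| 0.02 | 0.5 | 1.214 | 0.075 |
| 0.02 | 0.8 | 0.914 | 0.040 |

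Decaying correlation raises these by up to about 0.01. Other recalculations put the low end at ICC 0.05 at 0.16.

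Simulation of the logit models with CAC 0.8 and no IAC (2000 runs fixed-effects, 250 runs mixed model):

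- ICC 0.05: fixed-effects 0.256, mixed model 0.276.
- ICC 0.02: fixed-effects 0.129, mixed model 0.156.

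With CAC 1 and no IAC, the fixed-effects model rejects 0.05 of the time and the mixed model 0.08–0.10.

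**4. A test that can reject.** Regress the 12 cluster-quarter proportions on 3 cluster, 3 quarter and 1 treatment parameter: 12 − 7 = 5 degrees of freedom. Type I error is 5% under exchangeable correlation and about 3% under decay. For power, SE² = 1.2·[ICC × 0.2 × 0.125 + (1 − ICC)(1 − IAC) × 0.125/175]:

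- ICC 0.05: SE 0.0481 (IAC 0) to 0.0408 (IAC 0.8), power about 39% to 51%.
- ICC 0.02: SE 0.0379 to 0.0277, power about 56% to 82%.

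Decaying correlation, or simulating binary outcomes, lowers these; the lowest values found were about 25% and 43%. The overall ranges are about 25–50% and 43–82%.

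**The case against.** **The randomised unit is not entirely settled.** The Discussion speaks of randomising homes, and 30 orders would put 5% just within reach. The sections that describe the allocation itself all make the cluster the unit, and so does the timeline, so six orders apply. Under the home-level reading the test would still be close to powerless.

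**The fixed-effects model does help with the concern named.** This stands. With CAC 1 it holds about 5% where the mixed model does not. The inflation shown above comes from omitted cluster-by-period variation, a misspecification the primary model shares, and not only from the number of clusters.

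**The inflation depends on a quantity the article does not give.** This also stands. A reader might infer that the fixed-effects model always reproduces the primary model's error and would endorse any false positive. The documents do not support that. The cohort is closed, and at ICC 0.02 with IAC 0.8, the value that reproduces the stated power, its error is about 4%. At ICC 0.05, however, it is inflated at every IAC tried.

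**These are only sensitivity analyses.** True. No rule ties the conclusion to them, and their point estimates can still be informative. That limits the severity but does not make the sentence correct.

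**Conclusion.** The claim that these analyses deal with any concern about few clusters is wrong as written.

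The permutation part is exact, given three randomised clusters: the floor is p = 0.167 and power at 5% is zero. The fixed-effects part is conditional. Under the protocol's CAC of 0.8, type I error is about 16–25% at ICC 0.05 and about 4–13% at ICC 0.02, as IAC runs from 0.8 to 0. If CAC were 1, it would not be inflated.

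A reader might go further and conclude that neither analysis can tell us anything, or that the trial's conclusion falls with them. The documents do not support that: both are secondary and the primary analysis stands or falls separately. This should be fixed, but it is not a defect that by itself invalidates the plan.

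**What to change.** - Delete the sentence saying that these analyses address any concerns about the number of clusters.
- If the permutation test is kept, state in advance that its p-value cannot be below 0.167, and report it only as the rank of the observed rollout order among the six. Bring the Discussion's home-level wording into line with the allocation sections.
- Keep the fixed-effects model if wanted, but say that it does not allow for cluster-by-period variation.
- Add a regression of cluster-quarter proportions with cluster and quarter effects, testing the intervention on t with 5 degrees of freedom.

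The cost is a few sentences, with no extra data and no burden on residents. The downside should be stated openly: the added analysis has only about 25–50% power at ICC 0.05 and 43–82% at ICC 0.02, against the stated 72% and 96%, and is somewhat conservative (about 3%) if correlation decays over time. A non-significant result from it would therefore be weak evidence of no effect.
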